##### Other psychosocial outcomes

Retrospective data on a number of other psychosocial outcomes will be collected from the PSW+ group by M&E Buddies at six-month follow-up. These are categorical variables labelled “improved”, “no change” or “worsened”. We will present descriptive statistics showing proportion of participants in the PSW+ group who reported “improved” or “worsened” outcomes, for the following:
Marriage or romantic relationshipParenthoodRelationship with main caregiverRelationship with other family membersRelationship with hospital staff (not PSWs)Social relationships (e.g. friends, neighbours)Work or incomeEducation or trainingHousingHobbies or recreationPhysical health

#### Missing data

We expect attrition to be low, as the primary outcome data are derived from hospital records, meaning no follow-up contact with participants is required for the main analyses. The most likely reason for missing outcome data is loss of hospital records, which is not expected to affect the study groups differentially.

As per Schafer’s (1999) guidance, we will consider up to 5 % missing data to be inconsequential [63]. However, if more than 5 % of data is missing, then we will select appropriate principled missing data methods (e.g. multiple imputation), taking into consideration the data distribution and the mechanism, rate and pattern of missing data [64].

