Broadly defined, peer support is social emotional support that is mutually offered or provided by “peers”, people with lived experience of mental, neurological or substance use disorders [21, 24]. While peer support encompasses a wide range of different interventions, distinctions are made between formal peer support and informal peer support (or “naturally occurring” peer support, as described by Repper and Carter [2011, pp.393]) [24, 25]. Formal peer support is provided through peer-led programmes or by peers recruited to support roles in traditional mental health or social services [25]. Those offering formal peer support may refer to themselves as “peer support workers” (PSWs) [26], though peer support roles can vary greatly. (For example, the American trial described above employed “peer mentors” to deliver formal peer support [22].) Regardless of their role specifications, PSWs are generally considered to be further along on the road to recovery—able to manage their illness and pursue fulfilling lives—and thus able to leverage their personal experience of recovery to support others [18, 19, 24, 25, 27, 28].

The study described in this protocol is part of a broader evaluation of the Brain Gain II project in Uganda, one of the first LMICs to establish a formal peer support programme [29–31]. The aim of this study is to understand the impact of a formal peer support intervention delivered by trained PSWs on service users’ readmissions. The objective is to investigate whether frequent users of inpatient care who have access to peer support (PSW+) experience a greater reduction in rehospitalisation rates and number of days spent in hospital compared to those who do not have access to peer support (PSW-).

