### Setting

Butabika National Referral Hospital (“Butabika”) is a tertiary psychiatric facility with approximately 430 staff and 550 beds [36], though the number of inpatients often exceeds 750 and can approach nearly 1000 [15]. Butabika is located in a largely suburban area of southeastern Kampala, but patients from across Uganda access its services. Standard adult care consists primarily of on-site psychiatric and psychological interventions, and in some cases vocational training, as prescribed by hospital staff. Users in extremely vulnerable situations may be referred to a social worker for additional assistance. After discharge, users typically return to Butabika for outpatient services, attend one of four monthly community outreach clinics (each located within a 20 km radius of the hospital), or access mental health services at district hospitals closer to their homes.

Brain Gain II is a project of the Butabika Link in Uganda—a partnership between Butabika and the East London National Health Service Foundation Trust (ELFT) in the United Kingdom [31]. Brain Gain II aims to reduce the burden on inpatient care at Butabika by promoting recovery among service users on the hospital wards and following discharge. The two main components of Brain Gain II include: (1) establishing an on-campus Recovery College at Butabika, where people with lived and/or professional experience of mental or neurological disorders co-design and co-deliver a recovery-oriented training curriculum; and (2) offering formal peer support by trained PSWs to frequent users of psychiatric inpatient care at Butabika, on five hospital wards and in local communities in four districts [37].

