### Outcomes

For variables to be included in the primary analysis, Table 2 summarises the time-points for assessment, the form used and the data collector responsible.

**Table 2 Tab2:** Assessment of Outcome Variables and Confounders for Primary Analysis

Variable type	Variable	Assessment	Time point	Data source	Method of Assessment
**Outcomes**	• Hospital days • Rehospitalisations	Baseline	Point of referral	Secondary data from paper-based records	Data extracted from patient file and entered into referral form by ward staff, then checked by M&E Officer
		Follow-up	Six months from referral	Secondary data from paper-based records	Data extracted from patient file and entered into six-month admissions form by M&E Officer
**Confounders**	• Disability • Family support	Baseline	Initial ward visit after referral	Primary data collected via questionnaire (based on WHODAS 2.0 and MIND ME)	Reported by user to M&E Buddy using baseline form

There are two primary outcomes for this study, both related to change in frequent users’ utilisation of inpatient care at Butabika. The first is change in the number of hospital days over the previous six months. The second is change in the number of rehospitalisations over the previous six months. The index hospitalisation during which the participant was recruited into the study is excluded from both calculations. The study flow chart in Fig. 2 further illustrates the sequence of assessments in each group.

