#### Hospital days

Hospital days are the number of days spent in psychiatric inpatient care at Butabika over the previous six months. In order to calculate the number of hospital days, dates of entry and departure are extracted from the patient file at the point of referral and six months from referral. An entry may be the result of formal admission or return to the hospital’s premises following an escape. Similarly, a departure may be the result of formal discharge or escape from the hospital’s premises.

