#### Number of rehospitalisations

Number of rehospitalisations is the overall number of inpatient stays at Butabika over the previous six months. An inpatient stay is defined as a period of time spent in psychiatric inpatient care at Butabika and is also derived from the entry and departure data extracted from the patient file at the point of referral and six months from referral.

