Unfortunately, a randomized control trial was not deemed acceptable for the purposes of this study. Indeed, researchers in HICs have pointed out that randomisation may be in opposition to the principles of self-determination embraced by peer support programmes [71], though some have carried out successful randomised-controlled trials nonetheless. DID is designed to control for time-invariant and group-invariant confounders, but does not entirely eliminate the possibility of confounding or other types of bias. As noted by Wing, Simon and Bello-Gomez (2018): “The DID design is not a perfect substitute for randomized experiments, but it often represents a feasible way to learn about causal relationships” (pp.453).

The study design outlined in this protocol introduces a risk of bias, as the two study groups differ by district of residence. There is a possibility that unmeasured time- and group-variant factors may differ between districts and confound the relationship between peer support and use of inpatient care. Peer support is only available in four districts of the relatively prosperous Central and Eastern regions near the country’s capital city, Kampala, where Butabika is located. Further, this is not a blinded study, though PSWs responsible for delivering the intervention do not collect study data from their assigned peers, and neither PSWs, M&E Buddies nor the Peer Support Office Administrator have access to admissions data.

In addition, the outcomes compared between groups are limited to those which can be assessed using the hospital’s routinely collected data. Loss-to-follow-up after discharge from inpatient care is a significant issue for Butabika, which PSWs help to remedy through regular visits to the community. The comparison group does not have contact with PSWs after discharge. Therefore, stakeholders deemed it unfeasible to collect primary data from a significant number of participants in the comparison group. The Indian evaluation upon which this study is based faced similar challenges; outcomes could not be assessed in about a third of all participants in the comparison group [43].

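### A participant who dies, moves away or is admitted elsewhere after referral scores zero Butabika use rather than missing, and the missing-data rule cannot detect this possibly differential loss

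*Protocol article*

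**What the plan says.** The protocol restricts both primary outcomes to one hospital. Under Hospital days: "Hospital days are the number of days spent in psychiatric inpatient care at Butabika over the previous six months". Under Number of rehospitalisations: "Number of rehospitalisations is the overall number of inpatient stays at Butabika over the previous six months". The Outcomes section introduces them together as change in "utilisation of inpatient care at Butabika". The objective at the end of the Background has no such limit: it asks whether users with access to a peer support worker "experience a greater reduction in rehospitalisation rates and number of days spent in hospital".

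The Missing data section expects low attrition because outcomes come from hospital records, "meaning no follow-up contact with participants is required for the main analyses". It then names one likely cause of missing data: "The most likely reason for missing outcome data is loss of hospital records, which is not expected to affect the study groups differentially". Up to 5% missing is treated as inconsequential; above that, a principled method such as multiple imputation is chosen.

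Three other statements bear on this:
- **Setting.** After discharge, users typically return to Butabika as outpatients, attend its outreach clinics, "or access mental health services at district hospitals closer to their homes".
- **Setting and Selection.** The four peer-support districts lie within roughly two hours' drive of Butabika. The comparison group is everyone who lives elsewhere.
- **Discussion.** "Loss-to-follow-up after discharge from inpatient care is a significant issue for Butabika, which PSWs help to remedy through regular visits to the community". Participants in PSW- have no such contact once discharged.

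**The concern.** Finding the file is not the same as observing the participant. Someone who dies in month two, moves away, or is admitted to another hospital leaves a complete Butabika file with no later entry. That file is read as zero days and zero stays. It is not missing, so neither the 5% threshold nor multiple imputation applies to it.

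This matters most if it differs between groups and arises after referral. Distance, the option of care nearer home, and peer support workers keeping only the PSW+ group in touch all make a difference plausible. Entry requires three or more Butabika stays in the previous 24 months, so everyone was using Butabika before referral, and death or relocation can only happen afterwards. A gap of this kind enters the group-by-time interaction, which the Primary analysis section names as the effect of interest. Unseen use in the PSW- group would make peer support look less effective than it is. In either group, a death would look like a success. The Methods also describe a linked cost analysis of savings from fewer readmissions, which needs the same distinction between less hospital use and less use of this hospital.

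**Working it through.** **The plan's own figures.** The Missing data section has no figure to reproduce. The related one is in Study size: 180 × (1 − 0.15 − 0.15) = 126 PSW+ completers, which matches. That section therefore assumes 15% loss to follow-up, while the Missing data section expects attrition to be low. Neither gives a rate of use unseen by Butabika.

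**Inputs.**
- Target effect: 20% (Study size), read here as a true ratio of 0.80. This reading is an assumption, because the protocol cites Cohen and may mean a standardised effect.
- Unseen share of follow-up use: assumed 5% in PSW+ (q+) and 10%, 15% or 25% in PSW- (q−).

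**Formula.** If recorded use = true use × (1 − q), with subscript 0 for baseline and 1 for follow-up:

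recorded ratio = true ratio × [(1 − q1+)/(1 − q0+)] ÷ [(1 − q1−)/(1 − q0−)]

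**Case A: full capture at baseline, loss at follow-up only** (q0+ = q0− = 0).

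| q+ / q− | No true effect | True ratio 0.80 |
|---|---|---|
| 5% / 5% | 0.95/0.95 = 1.00 | 0.80 |
| 5% / 10% | 0.95/0.90 = 1.06 | 0.80 × 0.95/0.90 = 0.84 |
| 5% / 15% | 0.95/0.85 = 1.12 | 0.80 × 0.95/0.85 = 0.89 |
| 5% / 25% | 0.95/0.75 = 1.27 | 0.80 × 0.95/0.75 = 1.01 |

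The effect vanishes when 1 − q− = 0.80 × 0.95 = 0.76, that is, q− = 24%.

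If power were exactly 80% for a ratio of 0.80, the implied standard error of the log ratio would be 0.2231/(1.960 + 0.842) = 0.0797. At recorded ratios of 0.84, 0.89 and 1.01, power would be about 56%, 29% and 2%. This is only an illustration: the protocol's power inputs are in Additional file 2, which is not shown.

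**Case B: capture differs by group but is the same in both periods.** The terms cancel and the recorded ratio equals the true ratio. On the additive scale they cancel only if true use does not change. Take true stays falling from 1.0 to 0.7 in both groups, with q+ = 5% and q− = 25%:
- PSW+ change: 0.95 × (0.7 − 1.0) = −0.285
- PSW- change: 0.75 × (0.7 − 1.0) = −0.225
- Difference: −0.06 stays, in favour of peer support.

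The scale is not settled: the Primary analysis section starts from linear regression and allows a Poisson or negative binomial model if the data are skewed. The direction and size of any bias therefore depend on when the gap arises and on which model is used.

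**The case against.** The strongest defence is that Butabika use is the declared outcome, consistent with the programme's aim of relieving inpatient care there. For that outcome, an admission elsewhere is a true zero. This stands. Admission elsewhere matters for the wider objective, not as a recording error. It does not answer death or moving away, which shorten the time at risk under either reading.

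A reader might infer that the protocol declares all missingness to be the same in both groups and that its other sections prove the opposite. It does neither. The sentence concerns loss of records, and nothing suggests that files are lost more often in one group. The line on district hospitals sits among post-discharge options, does not mention inpatient admission, and describes users in general. PSW- users also reached Butabika three or more times despite the distance. A differential loss is a reasonable inference, not a documented fact.

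It is also tempting to use the protocol's 15% loss to follow-up, or the third of comparison participants not assessed in the Indian evaluation, as the rate of unseen PSW- admissions. Neither is one. The first is a planning figure applied to PSW+ enrolment. The second is cited to explain why collecting primary data from the comparison group was thought unfeasible.

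Finally, the Discussion concedes district-related confounding and reliance on routine data, and the analysis plan, not shown, may deal with death and time at risk. Those concessions are general. The article does not say that unseen use, death or moving scores as zero, and the missing-data reasoning it does print passes over them.

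**Conclusion.** The point holds as a gap in the outcome and missing-data reasoning. It is not a demonstrated bias. With the outcomes and data source as stated, loss of observation after referral is scored as zero use, and the stated rule cannot pick it up. It may plausibly differ by group. If it arises at follow-up only, with 5% unseen in PSW+ and 10% to 25% in PSW-, the interaction ratio moves by about 6% to 27%, comparable with the 20% effect the study is sized for. If the gap is stable over time, the ratio estimate is unaffected and an additive estimate may lean the other way. All the unseen shares are assumptions. This is a cheap improvement that narrows and protects what the study can conclude; it does not invalidate the design.

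**What to change.** 1. **Wording.** Keep the sentence on record loss. Add that unseen use, death and moving away are a separate source of error that may differ by group. State the objective (Abstract and Background) and the conclusions as Butabika days and Butabika rehospitalisations.
2. **Data.** On the six-month admissions form, have the M&E Officer take from the same file the date of last documented contact and any documented death, transfer or care elsewhere. Report these by group. Use observed time at risk as an offset in a sensitivity analysis, and note that ascertainment may itself differ, since a death in PSW- is less likely to reach the file.
3. **Tipping point.** Pre-specify an analysis over a grid of assumed unseen shares in both groups, and report the combinations at which the conclusion changes. It should replace some zero counts with positive ones as well as scale observed counts, because scaling leaves a false zero at zero.
4. **Supportive analysis only.** Repeat the primary analysis with PSW- limited to districts nearer Butabika, using the recorded district of residence.

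The cost is a few form fields read from a file already opened, some added sensitivity analyses, and a narrower claim. Item 4 loses precision: PSW- is planned at 87 followed up, and no district counts are given. No participant contact is needed.

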### Data quality

Although this study was not resourced to enable double data entry, we will undertake a number of other precautions to improve data quality. As described above, forms used for data collection are routinely checked for quality by the Brain Gain II M&E Officer, and performance-based incentives are also offered to staff for complete and accurate extraction of admissions data. Data validation rules are programmed into the spreadsheet used for data entry. We will carry out additional range and consistency checks during data cleaning.

At the conclusion of the six-month follow-up period, we will also perform a data quality audit. The primary investigator will sample every fourth participant file and check each paper form against a checklist for missing, illegible or illogical data. Data quality issues will be disaggregated by type and tabulated by data collector and question, to identify any common patterns. At the stage of data analysis, we will use either box-plots or z-scores to identify outliers. Where outliers are clearly the result of spurious data, corrections will be made if possible; otherwise, outliers resulting from spurious data may be treated as missing data.

## Ethics

This study was approved as part of a broader evaluation protocol for Brain Gain II. Institutional approval was received from the Research and Training Committee of the Butabika National Referral Hospital in Uganda. Ethics approval was secured from the London School of Hygiene and Tropical Medicine Research Ethics Committee in the United Kingdom (Ref 10,705) and Mengo Hospital Research and Ethics in Uganda (Ref 906/7). The evaluation protocol was also approved by the Uganda National Council of Science and Technology (Ref HS12ES). Additional details on the ethical considerations and procedures for this study are available from the study authors upon request.

## Discussion

This study will contribute to the evaluation of one of the first formal peer support programmes to be established in a LMIC. Given the high cost of inpatient care, the outcomes are particularly relevant to mental health policy in Uganda and other LMICs, where most government expenditure on mental health continues to be spent on psychiatric hospitals [23].

The use of a quasi-experimental study design is an improvement over previous evaluations of formal peer support in LMICs. Although formal peer support programmes have been established in statutory services in other LMICs such as China [65] and India [66], to the best of our knowledge, only one has published a quantitative evaluation of user-level outcomes. These outcomes were limited to change in mood and social communication skills, assessed retrospectively at a single time-point, with no comparison group [65, 67].

This is also one of remarkably few examples in which the manpower and unique expertise of people with lived experience of mental and neurological disorders is harnessed for the purposes of conducting evaluation research in a LMIC. A systematic review published in 2016 identified only one previous example; it came from Brazil, an upper-middle income country, and users were not involved until data had already been collected [68, 69]. A 2017 survey on psychosocial disabilities and barriers to participation in North India may have involved data collectors with psychosocial disabilities, although this is unclear from the study’s text [67, 70]. While engagement of M&E Buddies in data collection is desirable from an inclusion perspective, and may be more sustainable than relying on external evaluators, the use of M&E Buddies has not yet been tested in this context. Future publications will report not only on the outcomes of peer support in Uganda, but also on learning from the engagement of peers in the conduct of this study.

Unfortunately, a randomized control trial was not deemed acceptable for the purposes of this study. Indeed, researchers in HICs have pointed out that randomisation may be in opposition to the principles of self-determination embraced by peer support programmes [71], though some have carried out successful randomised-controlled trials nonetheless. DID is designed to control for time-invariant and group-invariant confounders, but does not entirely eliminate the possibility of confounding or other types of bias. As noted by Wing, Simon and Bello-Gomez (2018): “The DID design is not a perfect substitute for randomized experiments, but it often represents a feasible way to learn about causal relationships” (pp.453).

The study design outlined in this protocol introduces a risk of bias, as the two study groups differ by district of residence. There is a possibility that unmeasured time- and group-variant factors may differ between districts and confound the relationship between peer support and use of inpatient care. Peer support is only available in four districts of the relatively prosperous Central and Eastern regions near the country’s capital city, Kampala, where Butabika is located. Further, this is not a blinded study, though PSWs responsible for delivering the intervention do not collect study data from their assigned peers, and neither PSWs, M&E Buddies nor the Peer Support Office Administrator have access to admissions data.

In addition, the outcomes compared between groups are limited to those which can be assessed using the hospital’s routinely collected data. Loss-to-follow-up after discharge from inpatient care is a significant issue for Butabika, which PSWs help to remedy through regular visits to the community. The comparison group does not have contact with PSWs after discharge. Therefore, stakeholders deemed it unfeasible to collect primary data from a significant number of participants in the comparison group. The Indian evaluation upon which this study is based faced similar challenges; outcomes could not be assessed in about a third of all participants in the comparison group [43].

Finally, it is worth acknowledging that formal peer support can be challenging to implement [72]. For example, there is a risk that formalisation of peer support roles may actually reinforce hierarchical relationships in statutory services and ultimately undermine core peer support values [73]. At the same time, PSWs may be expected to serve as “carriers of a recovery culture into mental health systems” (Ibrahim 2019, n.page), resulting in conflict between PSWs and organisations resistant to change [72]. These are tricky relationships for PSWs to negotiate, even in relatively well-resourced settings. Meanwhile, resource limitations have been identified as major barriers to service user involvement in mental health systems strengthening in Uganda [74] and in LMICs more broadly [75]. While the Brain Gain I pilot demonstrated that it is feasible to deliver formal peer support in Uganda [31], there is always the possibility of “implementation failure” (Patton 2008, pp. 310) leading to null results [76]. In this case, our multi-method, Theory of Change-driven approach to the broader programme evaluation (described elsewhere [34, 35]) may help to identify “what went wrong” on the anticipated pathway of change and make targeted recommendations for future implementation.

In conclusion, this is a quasi-experimental DID study subject to a number of different constraints and potential biases, which should be followed up with more robust research, assessing more outcomes with locally validated measures, and ideally using a randomised design. Due caution will need to be taken in the interpretation of results. However, given the paucity of research currently available from LMICs, this study represents a crucial next step toward the development of a global evidence base for peer support.

